## PROTOCOL

**Vitamin D Intervention in Infants (VIDI)** is a large randomised trial that aims to evaluate effects of two vitamin D supplemental doses in early childhood on bone strength, infections, immunity, allergy, atopy and asthma, neurologic and cognitive development, and genetic regulation of mineral homeostasis.

This protocol comprises the applied methods to evaluate the effects of vitamin D supplementation on the primary outcomes of the study: bone strength and incidence of infections during the first two years of life. Methods for additional outcomes have been described in Helve et al, 2017.

### Background

Both cutaneously synthesised and vitamin D obtained from diet and supplements contribute to circulating 25-hydroxyvitamin D concentrations. The optimal 25-hydroxyvitamin D concentration is still under discussion. In 2011, Institute of Medicine guidelines stated that 25-hydroxyvitamin D concentrations above 50 nmol/L are required for normal body functions, including linear growth and bone mass accrual. According to the Endocrine Society, concentrations above 75 nmol/L may be necessary to achieve optimal long-term health benefits.

In Finland, Vitamin D supplementation has been recommended to all infants since the 1940's, but in line with the declining prevalence of rickets in our country, the recommended doses have gradually decreased. The present Finnish Nutritional Council guidelines recommend 10 µg (400 IU) of vitamin D3 supplementation daily for all infants from the age of 2 weeks to 2 years. Despite these recommendations, 20 % of 14-month-old children are shown to be vitamin D deficient (< 50 nmol/L).

Normal bone development and growth requires adequate intake of minerals, such as calcium and phosphate. Parathyroid hormone and biologically active form of vitamin D, 1,25-dihydroxyvitamin D, regulate calcium and phosphate concentrations. In addition, 1,25-dihydroxyvitamin D has direct effect on bone cells. Insufficient vitamin D supply results in inadequate bone mineralisation at growth plates and leads to rickets. In infants, severe vitamin D deficiency (< 25 nmol/L) associates with poor linear growth and delayed motor development possibly due to muscle weakness. Correction of vitamin D deficiency has been shown to improve growth velocity and prevent stunted growth. Data on the relationship between vitamin D and bone mineral density (BMD) in children are contradictory and further studies are essential.

In addition to its skeletal effects, vitamin D modulates both the innate and adaptive immune systems. Immune cells express vitamin D receptor (VDR) and have local enzymatic capacity to synthesise active 1,25-dihydroxyvitamin D. Vitamin D induces production of antimicrobial peptides, such as cathelicidin, by monocytes and macrophages, and is involved in regulation of T-lymphocyte function.

In epidemiological studies, vitamin D deficiency has been associated with increased risk of infections both in adults and children. Results from randomised trials are inconclusive. For example, in Japan, a daily supplemental vitamin D3 dose of 30 µg (1200 IU) for 4 months resulted in a significant reduction of influenza A infections, and in Mongolia, daily 7.5 µg (300 IU) of vitamin D3 reduced the risk of acute respiratory infections in schoolchildren. However, in Afghan infants, the incidence of pneumonia was not affected by 18 months of vitamin D supplementation. Further studies are needed to determine whether vitamin D supplementation provides benefits against infections in healthy children.

### Primary outcomes

Primary outcomes of the study are bone strength measured by peripheral quantitative computed tomography (pQCT) and incidence of parent-reported infections at age 2 years.

### Participants and methods

A total of 1 000 families are recruited and informed consent is obtained 1-2 days after the delivery at the Kättilöopisto Maternity Hospital in Helsinki. We include white northern European women with a singleton pregnancy and without regular medication. Healthy infants born at term (37-42 weeks) and with weight appropriate for gestational age are included in the study. Exclusion criteria for the infants are: seizures, need for early antibiotic

treatment, need for nasal continuous positive airway pressure > 24 hours, extended phototherapy > 72 hours, need for nasogastric tube > 24 hours or intravenous glucose infusion. Data on family background (parents' socio-economic status, health, lifestyle factors) and maternal dietary status are documented with a questionnaire. At birth, a cord blood sample (20 ml) is taken and stored for later analyses.

Participating infants are randomised to receive either the currently recommended vitamin D3 supplementation of 10 µg (400 IU) daily or a higher dose of 30 µg (1200 IU) daily from age 2 weeks to 2 years. Boys and girls are randomised separately in blocks of 50. Randomisation is performed by the Helsinki University Hospital Pharmacy. The study is double-blinded. Vitamin D is administered orally as vitamin D3, with a dose of 5 drops a day for both concentrations.

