## STATISTICAL ANALYSIS PLAN

### Sample size calculation and statistical analyses

We aim at detecting a 0.2 SD unit difference between continuous bone strength parameters; bone mineral content and cross-sectional area. In order to reach a statistical power of 90% with significance level of 0.05, a total of 210 and 297 measurements, respectively, are necessary. In addition, challenges in measuring infants with pQCT may occur. According to previous studies, small children suffer from an average of 6 infections annually. In order to detect a decrease from 12 to 9 infections during the 24-month study period, a sample size of 220 in each group is required. We estimate a possible drop-out rate of 20%. Taking into consideration all the aforementioned aspects, the trial is designed for 1000 subjects: 500 subjects in each intervention group.

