### Statistical methods

Comparisons between two intervention groups are analysed with independent samples t-test, Mann Whitney U-test or Pearson Chi-square as applicable. If possible, logarithmic transformation for non-normal variables is performed in order to achieve normal distribution. The impact of vitamin D supplementation, and relevant covariates, on serum 25-hydroxyvitamin D concentration is analysed with linear mixed model. For continuous variables (bone strength), differences between intervention groups are assessed with multivariate analysis of covariance (MANCOVA). For evaluating the effect of vitamin D supplementation on the frequency of infections, negative binomial model is applied. Infection incidence is estimated as proportion of follow-up time as person-months allowing utilisation of all available data. Main outcome measures are analysed according to intention-to-treat and protocol-based manner.

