### STATISTICAL ANALYSIS PLAN

#### Statistical methods

Standard statistical methods such as linear and logistic regression with SPSS software will be used to study the impact of vitamin D supplementation and/or maternal 25(OH)D concentrations, and relevant covariates, on main outcomes.

If needed, logarithmic transformation will be used to normalize skewed variables. Outcome measures will be analyzed according to the intention-to-treat principle.

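### Randomisation is stratified by sex, but the plan pre-specifies sex as a covariate in no treatment comparison

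*Combined protocol and SAP*

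**What the plan says.** **Allocation.** Protocol, Participants and methods: "Boys and girls are randomised separately in blocks of 50". Sex is the only stratification factor described.

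**Main SAP, Statistical methods.** The general sentence reads "Comparisons between two intervention groups are analysed with independent samples t-test, Mann Whitney U-test or Pearson Chi-square as applicable"; none of these tests carries a covariate. Bone strength is then assigned to a MANCOVA whose covariates are not named. For the other primary outcome, "For evaluating the effect of vitamin D supplementation on the frequency of infections, negative binomial model is applied"; follow-up time in person-months is the only other element mentioned. The mixed model for serum 25-hydroxyvitamin D admits covariates without listing them.

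**Neurodevelopment amendment, Statistical methods.** Linear, logistic, Tobit and moderation analyses of ASQ and ITSEA, with covariates left undefined.

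**Current-study amendment, Statistical methods.** Linear and logistic regression of CBCL on supplementation "and/or maternal 25(OH)D concentrations, and relevant covariates, on main outcomes". The section on psychiatric symptoms converts CBCL scores to T-scores specific to sex and age before they are dichotomised.

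Sex appears as a model term in none of these sections.

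**The concern.** Randomising boys and girls separately forces the arms to have nearly the same sex mix. Variation between the sexes then contributes almost nothing to the difference between arms. A standard error computed without sex still counts that variation. If the outcome differs by sex, the standard error is too large, the confidence interval too wide, the true type I error below the nominal 5%, and some power is lost.

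The general remedy is to analyse by the factor used to randomise. Here sex is known for every child at randomisation, so nothing has to be collected. Leaving the covariates undefined also lets the analyst choose between a sex-adjusted and an unadjusted result after seeing the data. For logistic models that choice changes the quantity estimated, not only its precision.

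**Working it through.** **The plan's own figures.** No sample size in the plan depends on sex, so there is no stated figure to reproduce on this point. The main SAP does say: "We aim at detecting a 0.2 SD unit difference between continuous bone strength parameters; bone mineral content and cross-sectional area" and "In order to reach a statistical power of 90% with significance level of 0.05, a total of 210 and 297 measurements, respectively, are necessary". For two groups, two-sided, n per arm = 2(1.960 + 1.282)² / 0.2² ≈ 526, or 1052 in total; one-sided it is 429 per arm. Neither gives 210 or 297. That is a separate matter and is not used below.

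**Inputs.**
- Main SAP, sample size section: "the trial is designed for 1000 subjects: 500 subjects in each intervention group", with 20% drop-out, so 500 × 0.8 = 400 per arm analysed.
- Same section: effect 0.2 SD (taken here as within-sex SD) and alpha 0.05 (taken as two-sided; the plan does not say).
- Boy-girl difference d, in within-sex SD: **not in the documents**, so varied from 0.2 to 1.0, with half the children boys.

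**Formulas for a continuous outcome.** With sex balanced, the standard error of the treatment difference in within-sex SD units is √(2/400) = 0.0707. The unadjusted test uses a variance too large by the factor 1 + d²/4. Hence:
- sex-adjusted power = Φ(0.2/0.0707 − 1.960) = Φ(0.868) = 80.7%, with alpha 0.050;
- unadjusted alpha = 2[1 − Φ(1.960√(1 + d²/4))];
- unadjusted power = Φ(2.828 − 1.960√(1 + d²/4)).

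| d (assumed) | 1 + d²/4 | effective critical value | true alpha | power, unadjusted | loss (points) |
|---|---|---|---|---|---|
| 0.2 | 1.010 | 1.970 | 0.0489 | 80.5% | 0.3 |
| 0.3 | 1.0225 | 1.982 | 0.0475 | 80.1% | 0.6 |
| 0.5 | 1.0625 | 2.020 | 0.0434 | 79.0% | 1.7 |
| 0.8 | 1.160 | 2.111 | 0.0348 | 76.3% | 4.4 |
| 1.0 | 1.250 | 2.191 | 0.0284 | 73.8% | 6.9 |

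With all 500 per arm analysed, adjusted power is 88.5% and the losses at d = 0.3, 0.5 and 0.8 are 0.4, 1.2 and 3.2 points.

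**Check by simulation.** 1000 children were randomised in blocks of 50 within sex, 20% were lost at random, and a t-test was compared with a linear model including sex (10,000 replicates for alpha, 5,000 for power).

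| d | alpha, unadjusted / adjusted | power, unadjusted / adjusted |
|---|---|---|
| 0.2 | 0.0488 / 0.0497 | 80.8% / 81.1% |
| 0.5 | 0.0438 / 0.0500 | 78.5% / 80.2% |
| 0.8 | 0.0405 / 0.0522 | 75.3% / 80.6% |
| 1.0 | 0.0331 / 0.0495 | 73.7% / 81.2% |

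Direction and size agree. At large d the simulated alpha lies somewhat above the formula. The formula assumes exact sex balance among analysed children, and losing 20% at random restores about a fifth of the between-sex variance. At d = 0.8 the factor becomes 1.16 / (1 + 0.2 × 0.16) = 1.124, the critical value 1.960 × √1.124 = 2.078, and alpha about 0.038; the Monte Carlo standard error is about 0.002. The formula's alpha is therefore a lower limit.

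**Infections and binary outcomes.** The SAP gives neither a sex effect nor a dispersion for infections, so no figure is offered there. In logistic regression the linear argument fails: adding a prognostic covariate does not shrink the standard error of the log odds ratio, and the adjusted odds ratio is a conditional quantity.

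**The case against.** **The plan may adjust for sex after all.** A reader might infer that no treatment comparison is adjusted for sex. The documents do not support that. MANCOVA is by name an analysis with covariates, and the ASQ/ITSEA and CBCL sections provide for covariates; sex may well be among them, in which case the loss computed above is zero for those models. This stands. What the documents show is that sex is not pre-specified, not that it is omitted.

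**The figures belong to a test that may not govern a primary outcome.** The sentence on t-tests can be read as general, with MANCOVA and the negative binomial model governing bone strength and infections. This largely stands, and the figures are offered only as the cost of leaving sex out of a linear analysis. It does not remove the point: the infection model, as written, has no covariate, so following the plan literally ignores the stratification factor for one primary outcome.

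**The size is assumed, small and in the safe direction.** This also stands. No boy-girl difference is given for any outcome; below 0.3 SD the loss is under one point, and only differences of 0.8 SD or more cost four points or more. A reader might infer false-positive findings or biased estimates; neither follows, since the alpha falls below 5% and sex is balanced by design.

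**In reply.** The bone comparison has little power to spare: at 400 per arm it has about 81% for 0.2 SD even with adjustment, against the 90% the SAP aims for. And the plan treats sex as relevant elsewhere, both in allocation and in CBCL scoring.

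**Conclusion.** The point holds as a gap in pre-specification. The factor used to stratify randomisation is named in no treatment comparison; adjustment is possible under the plan but not promised.

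If sex is omitted, tests on continuous outcomes are mildly conservative, with the losses tabulated above. Those figures rest on assumed sex differences, equal numbers of boys and girls, a two-sided 5% test, 400 per arm, and sex balance surviving drop-out. They should not be read as the loss for the infection, Tobit or logistic analyses. For CBCL little or no loss is expected, because the scores are already sex-specific.

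This is an inexpensive improvement that should be made. It is not a threat to the validity of the trial.

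**What to change.** **Main SAP and neurodevelopment amendment, Statistical methods.** State that the primary treatment-effect models for bone strength (MANCOVA), infections (negative binomial), ASQ and ITSEA include sex as a fixed covariate because randomisation was stratified by sex. State also that these models replace unadjusted t-tests or chi-square tests for those outcomes.

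**Logistic models.** State that the sex-adjusted (conditional) odds ratio is the reported estimate.

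**Current-study amendment.** Sex may be included in the CBCL models for consistency, without expecting much gain.

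**Cost.** A sentence or two of SAP text and one covariate already recorded; no new data and no change in sample size. For any outcome whose analysis is already complete, the sex-adjusted model can be reported as a labelled sensitivity analysis.

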### **Follow-up**

Participants are assessed at a study outpatient clinic by a study nurse and/or pediatrician at 6 months, 1 year and 2 years of age. Growth parameters (length, weight, head circumference) are measured and compared with Finnish growth charts. Blood samples are taken for biochemistry. Bone strength of participants is evaluated by pQCT at 1 and 2 years of age. Families are provided study diaries where they keep daily records on dosing of vitamin D3 supplement and on all infections of the participating child. Nutrient intake from food is evaluated from 3-day food record at 1 year and a Food Frequency Questionnaire (FFQ) at 2 years of age.

### **Specific methods**

#### *Biochemical markers*

Serum 25-hydroxyvitamin D concentration is measured from serum samples with an automated IDS-iSYS analyser (IDS Ltd., Bolton, UK) which employs a chemiluminescence immunoassay (CLIA) with high sensitivity, a fast protocol, with a 10-µl specimen volume. The method is validated against LC-MS in-house as well as by the manufacturer. Analyses are performed at the Pediatric Research Centre laboratory in Biomedicum, University of Helsinki (Helsinki, Finland). Reproducibility is ensured by adhering to the Vitamin D External Quality Assessment Scheme (DEQAS, Charing Cross Hospital, London UK). The IDS-iSYS immunoassay will also be used to analyse serum intact parathyroid hormone concentration from serum samples.

Ionised calcium (adjusted to pH 7.40, normal range 1.16-1.39 and 1.17-1.35 mmol/L for age groups 1-12 months and 24 months respectively) is analysed from capillary blood samples at 6 months and from serum samples at 12 and 24 months at the Central Laboratory of Helsinki University Hospital (HUSLAB) using ABL 90 FLEX or ABL 835 FLEX blood gas analysers. HUSLAB is an accredited laboratory adhering to international (T055) SFS-EN ISO 15189 and SFS-EN ISO/IEC 17025 standards.

#### *Bone strength*

Bone strength is measured by pQCT from the distal left tibia using a XCT-2000 scanner (Stratec Medizintechnik GmbH, Pforzheim, Germany).

#### *Infections*

Data on infections are collected prospectively from daily diaries kept by parents of participating infants. Parents record the time and duration of the infection, symptoms, required medication, physician visit or hospitalisation in the daily diaries. Every 3-6 months, new diaries are provided to the families by mail or at follow-up visits, and completed diaries are returned to the study nurse.

#### *Dietary vitamin D intake*

At recruitment, maternal diet is evaluated retrospectively with a semi quantitative 22-item Food Frequency Questionnaire, for the time-period of one month before delivery. At age 1 years, data on nutrient intake from food is collected with a three-day food record and analysed using AivoDiet software (Aivo Oy Finland, Turku, Finland). At 2 years, the dietary habits of the child are collected with 47-item Food Frequency Questionnaire. If the child attends daycare, the personnel are asked to complete a separate two-day food record.

#### *Ethical issues and research permits*

A recent intervention study confirmed the safety of vitamin D supplementation in infants with a daily dose of 50 µg (2000 IU) daily. Furthermore, we conducted a pilot study in 113 healthy newborns in order to evaluate short-term effects and safety of 3 different vitamin D3 doses (10 µg, 30 µg, 40 µg daily). No adverse events occurred and all doses were deemed safe. Based on the results, we chose daily doses of 10 µg and 30 µg for the intervention study.

An external clinical research institute monitors the study and possible adverse effects. As a safety protocol, the infants are monitored for hypercalcemia at follow-up visits. If the calcium concentration exceeds the upper reference limit of ionised calcium by  $\geq 10\%$ , defined as ionised calcium concentration above 1.53 mmol/L at 6 and 12 months and 1.48 mmol/L at 2 years follow-up, the ionised calcium and 25-hydroxyvitamin D concentrations will be repeatedly measured, symptoms indicative of hypercalcemia will be evaluated, and, if necessary, dosing of vitamin D supplementation adjusted.

Blood samples are taken as follows: A) 20 ml from the umbilical vein after cord clamping at birth, B) 15 ml at age 1 year, and C)  $\leq 20$  ml at age 2 years. These volumes are clearly below the allowed maximal volumes for research sampling (approximate limits for research purposes are for ages 1 year: 24 ml and 2 years: 36 ml; i.e. 3% of circulating blood volume).

The radiation exposure from pQCT measurements is estimated to be 30 µSv, and exposure from whole-body DXA 50 µSv. This total dose of approximately 80 µSv equals radiation exposure during an overseas flight or 2 weeks' background radiation, and can thus be regarded as insignificant. Similar methods have previously been used to study bone variables in newborns.

The vitamin D3 supplements are provided by Orion Pharmaceuticals free of charge. The study is researcher initiated and independent.

Informed consent is obtained from the parents at recruitment. An ethical approval has been obtained from the Research Ethics Committee of the Hospital District of Helsinki and Uusimaa (ID 107/13/03/03/2012) including permission to keep a research register of collected data where the anonymity of all participants is secured with an identification number. Research permits from Children's Hospital are valid until 2018. The project protocol is registered into ClinicalTrials.com (NCT01723852).

## STATISTICAL ANALYSIS PLAN

### Sample size calculation and statistical analyses

We aim at detecting a 0.2 SD unit difference between continuous bone strength parameters; bone mineral content and cross-sectional area. In order to reach a statistical power of 90% with significance level of 0.05, a total of 210 and 297 measurements, respectively, are necessary. In addition, challenges in measuring infants with pQCT may occur. According to previous studies, small children suffer from an average of 6 infections annually. In order to detect a decrease from 12 to 9 infections during the 24-month study period, a sample size of 220 in each group is required. We estimate a possible drop-out rate of 20%. Taking into consideration all the aforementioned aspects, the trial is designed for 1000 subjects: 500 subjects in each intervention group.

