## STATISTICAL ANALYSIS PLAN

### Sample size calculation and statistical analyses

We aim at detecting a 0.2 SD unit difference between continuous variables (developmental milestones and social-behavioral problems and competencies) and Odds Ratios >2.0 in categorical variables (mild developmental delay, clinically possible significant problems). In order to reach statistical power of 80% with significance level of 0.05, a total of 199 and 572 participants, respectively, are necessary. The trial was designed with a planned sample of 1000 study participants. We estimate a possible drop-out rate of 20% for each follow-up.

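### Bone-strength sample size: the totals of 210 and 297 measurements cannot be reproduced from the stated 0.2 SD difference, 90% power and 0.05 level

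*Combined protocol and SAP*

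**What the plan says.** The main SAP, under Sample size calculation and statistical analyses, gives one target for two bone outcomes: "We aim at detecting a 0.2 SD unit difference between continuous bone strength parameters; bone mineral content and cross-sectional area". The requirement follows: "In order to reach a statistical power of 90% with significance level of 0.05, a total of 210 and 297 measurements, respectively, are necessary". The sentence cites a study of tibial bone strength in early childhood. It gives no test, sidedness, SDs, absolute differences or covariates.

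The same paragraph notes that pQCT may be difficult in infants, gives a separate infection calculation (220 per group), allows for 20% drop-out and, weighing all of this together, concludes that "the trial is designed for 1000 subjects: 500 subjects in each intervention group". It does not say what power 1000 children give for bone strength.

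Statistical methods in the main SAP plans MANCOVA for bone strength and names no covariates. The protocol's Primary outcomes section lists bone strength by pQCT as one of two primary outcomes, at age 2 years. Its Follow-up section schedules scans at 1 and 2 years.

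**The concern.** A difference of 0.2 SD is small, and detecting it between two groups with 90% power normally takes about a thousand children, not two or three hundred. It is also odd that a target in SD units produces two different numbers. Standardising removes the outcome's own scale, so at a common significance level and power the two outcomes should need the same number.

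This paragraph is the only power justification for bone strength. Someone who sets 210 and 297 beside a trial of 1000 would conclude that the design has a wide margin for drop-out and failed scans, and that an analysis of a few hundred valid scans is adequately powered for 0.2 SD. On the stated inputs neither is true.

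**Working it through.** **Inputs.** From the main SAP's sample-size paragraph: d = 0.2 SD for both outcomes; power 90%; level 0.05; 500 per group; drop-out 20%, leaving 500 × 0.8 = 400 per group. Sidedness is not stated, so two-sided is assumed and one-sided is also shown.

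**Attempt to reproduce 210 and 297.** For two equal groups, n per group = 2(z₁₋α/₂ + z₁₋β)²/d².

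- Two-sided: 2(1.960 + 1.2816)²/0.04 = 2 × 10.507/0.04 = 525.4, so 526. The exact t-test gives 526.3, so 527 per group and 1,054 in total.
- One-sided: 2(1.645 + 1.2816)²/0.04 = 2 × 8.564/0.04 = 428.2. The exact t-test gives 428.9, so 429 per group and 858 in total.

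Against 1,054, the stated totals are too small by factors of 1,054/297 ≈ 3.5 and 1,054/210 ≈ 5.0.

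Other readings:

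- *One-sample formula*, (z + z)²/d², exact t: 265 two-sided or 216 one-sided. The second is near 210, but it is not a between-group test and does not give 297.
- *Counting two scans per child.* If each child's 1- and 2-year values are averaged, with 0.2 SD at both visits and uncorrelated values, the need is about 525 children, or 1,051 measurements. A positive correlation raises it.
- *Joint test of both outcomes*, 0.2 SD on each: 90% power needs 636 children at outcome correlation 0 and 1,206 at 0.9.
- *Covariate adjustment*, N × (1 − R²): 210 needs R² = 1 − 210/1,051 = 0.80, and 297 needs R² = 1 − 297/1,051 = 0.72. The documents state neither.

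**Power at 0.2 SD.** Two-sided power ≈ Φ(d√(n/2) − 1.960). For 400 per group: 0.2 × √200 = 2.828; 2.828 − 1.960 = 0.868; Φ = 0.807. The difference detectable with 90% power is 3.2415 × √(2/n). Powers below are from the exact t-test, within 0.3 of a point of the formula.

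| Reading | n per group | Power at 0.2 SD | Detectable at 90% |
|---|---|---|---|
| 210 as a total | 105 | 30% | 0.45 SD |
| 297 as a total | 148.5 | 40% | 0.38 SD |
| 210 per group | 210 | 53% | 0.32 SD |
| 297 per group | 297 | 68% | 0.27 SD |
| 1000 less 20% | 400 | 81% | 0.23 SD |
| All 1000 evaluable | 500 | 88.5% | 0.205 SD |

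**Sensitivity of the last two rows.** One-sided, power is 88% at 800 children and 93.5% at 1000. With covariates, 90% is restored at 800 if R² = 1 − 800/1,051 = 0.24, and at 1000 if R² = 1 − 1,000/1,051 = 0.05. A joint test of both outcomes gives 95.6% down to 73.9% at 800, and 98.5% down to 83.5% at 1000, for correlations from 0 to 0.9.

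**The case against.** The strongest reply is that the planned analysis is MANCOVA, not an unadjusted t-test. Outcome-specific covariate adjustment could explain both the small numbers and the difference between them, and the inputs may lie in the cited bone study. This stands in part. It rules out saying that no calculation could yield 210 and 297, or that the two figures are proven to contradict each other; what they show is an input that is not reported. It does not rescue the sentence, which mentions no adjustment and would need R² of about 0.80 and 0.72.

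A reader might also infer that the full trial cannot reach 90% power for bone strength. The documents do not support that. The shortfall with all 1000 evaluable is 1.5 points, holds only for a two-sided unadjusted single-outcome test, and disappears with R² of about 0.05. Power under the planned MANCOVA is undetermined.

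Nor should the neurodevelopment amendment be used as proof. It says, for 0.2 SD and for odds ratios: "In order to reach statistical power of 80% with significance level of 0.05, a total of 199 and 572 participants, respectively, are necessary". Its 199 agrees with a one-sample t-test (198.2, rounded up), not with a two-group comparison (394 per group by t-test). It concerns other outcomes and other models, so setting it against 210 tests one doubtful figure with another.

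Finally, the trial size was not derived from 210 or 297 alone; infections, scan difficulty and drop-out were weighed too. That is correct, and it is why the remedy is confined to wording.

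**Conclusion.** The concern holds in a limited form: the stated requirement for a primary outcome is wrong as written, because 210 and 297 cannot be reproduced from 0.2 SD, 90% power, a 0.05 level and two groups. This does not depend on sidedness or on whether the figures are totals or per group; even one-sided, 429 per group are needed.

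The consequence for the trial is smaller than that gap suggests. After the plan's own drop-out, power for 0.2 SD is about 81% rather than 90%, before failed scans. That figure assumes a two-sided, unadjusted test of one outcome with 400 children per group.

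It may be tempting to add that the plan promises a null bone result would exclude 0.2 SD with 90% power. It makes no such statement: it gives an aim and a required number. The infection calculation is not affected by this point.

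**What to change.** Replace the sentence in the main SAP with:

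> For an unadjusted two-sided comparison at 0.05, detecting 0.2 SD in bone mineral content or cross-sectional area with 90% power needs 527 valid measurements per group. With 1000 randomised and 20% drop-out (400 per group), power for 0.2 SD is about 81% and 0.23 SD is detectable with 90% power, before failed scans and before any gain from covariate adjustment.

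Alternatively, if 210 and 297 rest on other inputs (absolute differences, SDs, a covariate R²), state them with the formula and sidedness, and drop or correct the 0.2 SD claim. Without adjustment the figures correspond to 0.45 and 0.38 SD as totals, or 0.32 and 0.27 SD per group.

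The cost is a change of SAP wording and a less favourable stated power. Enrolment and conduct are unchanged.
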